**Dose Adjustment Criteria**

| **Toxicities graded by NCI** | **Hematological toxicities** |
| --- | --- |
| Grade I | Maintain the original dose (appropriate symptomatic treatment should be provided). |
| Grade II | Maintain the original dose (appropriate symptomatic treatment should be provided). |
| Grade III | Initially, suspend the drug and aggressive symptomatic treatment should be performed, and maintaining the original dose if toxicity restores to grade <II. |
| Grade IV | Initially, suspend drug and aggressive symptomatic treatment should be performed, and downward dose adjustment should be performed if toxicity restores to grade <II. |
|  | **Non-hematological toxicities** |
| Grade I | Maintain the original dose (appropriate symptomatic treatment should be provided). |
| Grade II | Symptomatic treatment and continue drug treatment should be provided. If AE resolves to grade <I within 2 weeks, continue drug treatment; If AE does not improve or aggravate, drug interruption until AE resolves to grade <I and continue drug treatment with original dose level. |
| Grade III | Drug interruption and symptomatic treatment should be provided. If AE resolves to grade <I within 2 weeks, continue drug treatment with the original dose level or at a dose reduced by one level by the investigator's discretion; Drug interruption is recommended if a grade 3 or above adverse reaction occurs. |
| Grade IV | Drug interruption and symptomatic treatment should be provided, and the dose is reduced by one level if AE resolves to grade <I; Drug interruption is recommended if a grade V AE occurs (such as Grade V kidney injury, neurotoxicity, cardiotoxicity, hepatotoxicity, and other life-threatening). |
| **AEs of special interest** | |
| Once hypertensive intracerebral hemorrhage, intracerebral hemorrhage, pulmonary hemorrhage (≥grade II), other hemorrhages (≥ grade III), arterial thrombosis, venous thrombosis (grade IV), Leukoencephalopathy syndrome, and gastrointestinal perforation occur, drug interruption is recommended and aggressive symptomatic treatment should be provided. | |

- 1. **Dose adjustment of gefitinib**

If the patient exhibits intolerable diarrhea (generally associated with dehydration), skin toxic effects, or other AEs caused by gefitinib, briefly discontinuing (up to 42 days) of gefitinib may be performed and then resuming the dose to 250 mg/day for the patient.

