**Table 7.4.1. Classification criteria (NCI-CTC AE 4.0) and recommendations for prevention and treatment**

| Criteria | Definition | Prevention and treatment |
| --- | --- | --- |
| Grade I | SBP 120-139 mmHg, or DBP 80-89 mmHg | Close monitor of BP; Limit sodium intake, and quit smoke and alcohol; Continue to administer anlotinib without dose adjustment. |
| Grade II | SBP 140-159 mmHg, or DBP 90-99 mmHg | Close monitor of BP; Continue to administer anlotinib without dose adjustment; Treatment with antihypertensive drugs, and should not be stopped arbitrarily. |
| Grade III | SBP ≥160 mmHg, or DBP ≥100 mmHg | Suspension of anlotinib; Consider the combination of drugs for hypertension with poor control of monotherapy; Consult a cardiovascular specialist; Close monitor of BP; Continue the drug treatment at a dose reduced by one level with well-controlled blood event |
| Grade IV | Life-threatening (malignant hypertension or  Hypertensive emergencies/persistent neurological deficit) | Immediate and permanent drug discontinuation; Consult a cardiovascular specialist; Aggressive treatment and close monitor of BP and other vital signs |
| Grade V | Death | - |

1. **HFSR**

Patients should avoid mechanical trauma to hands and feet in the treatment, wearing loose-fitting comfortable shoes, softy cotton socks or gloves, and gel inserts, and vigorous exercise which may help limit the reaction; Avoiding direct sunlight on the skin, and using topical emollients or other preparations containing urea or lanolin to protect shin; Avoiding eating hot and spicy food. Treatment of moderate HFSR (if occurs) includes strengthening skin care by mild moisturizer or lubricant to keep the skin clean and moist and avoid secondary infection, pressure, or friction; Topical administration of exfoliating drugs may be administered (such as creams and ointments containing urea, 5% salicylic acid, and corticosteroid lotions), and dissolving the magnesium sulfate in warm water and soaking the affected skin if necessary; Topical antifungals or antibiotics; Appropriately administrating of B vitamins (B1, B6, and riboflavin) and celecoxib. If hyperkeratosis leads to thickened and calloused of foot skin, podiatrists can perform podiatric care to prevent further aggravation and use moisturizing ointment immediately after the pedicure.

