**Table 7.4.2. HFSR classification criteria (NCI-CTC AE 4.0) and recommendations for prevention and treatment**

| Criteria | Definition | Prevention and treatment |
| --- | --- | --- |
| Grade 1 | Minimal skin changes or dermatitis (e.g., localized erythema, hyperkeratosis, oedema, and painless), but not interfering with daily life | Continuing anlotinib administration without dose adjustment; Treating with topical medication at the first sign of symptoms. |
| Grade 2 | Significant skin changes (flaking, blisters, swelling, and hyperkeratosis) and pain, interfering with daily life and activities. | Continuing anlotinib administration with appropriate dose adjustment; Local drug; Oral B vitamins and celecoxib, and may combine with anti-inflammatory or anti-infective drugs. |
| Grade 3 | Severe skin changes (flaking, blisters, bleeding, ulcers, oedema, and hyperkeratosis) with significant pain and limited personal self-care ability. | Suspension of anlotinib; Analgesic management and topical treatment; Combination of anti-inflammatory or anti-infective drugs; Administering a lower dose of anlotinib if symptoms resolve; Discontinuing anlotinib if symptoms persist and worsen. |

1. **Proteinuria**

When grade >2 proteinuria occurs, the dose of anlotinib is interrupted and awaiting for recovering. If grade 2 or higher proteinuria occurs, continue drug treatment of anlotinib after a dose reducing by one level; if proteinuria persists and worsens, discontinue the drug.

In the event of renal insufficiency or nephrotic syndrome, the drug must be discontinued immediately and aggressive symptomatic treatment must be administered. There is no definitive treatment for proteinuria induced by anti-angiogenic inhibitors, but ACEI and ARB analogues may be administered as appropriate due to their ability in reducing intrarenal tubular pressure and thus proteinuria, as well as reduce possible cardiac AEs. Recommendations for the prevention and treatment of anlotinib-associated proteinuria can be viewed in Table 7.4.2 proteinuria classification criteria (NCI-CTC AE 4.0) and recommendations for prevention and treatment.

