**Table 7.4.3. Proteinuria classification criteria (NCI-CTC AE 4.0) and recommendations for prevention and treatment**

| Criteria | Definition | Prevention and treatment |
| --- | --- | --- |
| Grade 1 | Urokinase protein (+) or 24-hour urine protein excretion <1.0 g | Continuing anlotinib administration without dose adjustment |
| Grade 2 | Urokinase protein (++) or 24-hour urine protein excretion of 1.0-3.4 g | Continuing anlotinib administration without dose adjustment; Drug intervention should be considered; Monitor 24-hour urine routine and 24-hour urine protein excretion |
| Grade 3 | 24-hour urine protein excretion >3.4 g | Suspension of anlotinib; Consultation with a nephrologist specialist; Drug intervention should be performed; Dose reduction of anlotinib after recovery of proteinuria to ≤ grade 2; If grade 3 proteinuria still occurs after 2 dose reductions, anlotinib therapy should be permanently discontinued |

1. **Bleeding**

The PT and international normalized ratio (INR) should be closely monitored during the administration of anlotinib to monitor patients for bleeding tendencies and related symptoms; the drug should be interrupted if a grade 3-4 bleeding event occurs. If [upper gastrointestinal bleeding](https://www.sciencedirect.com/science/article/pii/S0025712508000023) occurs, anlotinib must be interrupted and aggressively treated according to clinical protocols should be performed.

1. **Thrombus**

If any arterial thrombosis (e.g., cerebral ischemia, stroke, angina, myocardial infarction) occurs, drug administration should be discontinued immediately and the study should be withdrawn. If symptomatic grade IV venous thrombosis occurs, drug administration should be discontinued in patients, with withdrawal from the study.

For patients with thrombotic symptoms, symptomatic treatment, surgery, or anticoagulant drugs should be scheduled immediately.

For patients with venous thrombosis, the criteria for dose adjustment are as follows:

| **Venous thrombosis** | **Dose adjustment** |
| --- | --- |
| Grade II | Anlotinib is maintained at the original dose level and closely monitored. |

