**QoL**

The changes in relevant clinical symptoms and objective examination results of patients before and after treatment were observed for scoring, and the scoring results of each domain of the scale were recorded in the eCRF according to the requirements of the quality of life scores. QoL is assessed by the EORTC QLQ-C30 (version 3) and EQ-5D.

- 1. **Safety analysis**
     1. **AEs**
        1. **Definitions of AEs**

AE is defined as any untoward medical occurrence in a patient or clinical investigation subject administered a pharmaceutical product and which does not necessarily have to have a causal relationship with this treatment. Any AEs that occur within 30 days from the initiation of the study drug to the end of treatment in this trial, regardless of whether or not have a causal relationship with this treatment, will be determined as AEs.

Investigators are required to record any AEs in subjects, including the events, AEs-related symptoms, time of occurrence, severity, duration, management, and outcomes.

- - - 1. **AEs grade**

The severity grade of any AEs will be assessed according to the definitions in NCI-CTCAE v4.0. For AEs that are not listed in the table, the following criteria can be referenced.

Grade I is defined as mild; asymptomatic or mild symptoms; clinical or diagnostic observations only; intervention not indicated.

Grade II is defined as moderate; minimal, local, or noninvasive intervention indicated; limiting age-appropriate instrumental activities of daily living (ADL, instrumental ADL refers to preparing meals, shopping for groceries or clothes, using the telephone, managing money, etc).

Grade III is defined as severe or medically significant but not immediately life-threatening; hospitalization or prolongation of hospitalization indicated; disabling; limiting self-care ADL (self-care ADL refers to bathing, dressing and undressing, feeding self, using the toilet, taking medications, and not bedridden).

Grade IV is defined as life-threatening consequences; urgent intervention is indicated.

Grade V is defined as death related to AE.

**Note:** For abnormal AEs or abnormal laboratory test indicators allowed by the inclusion criteria at the time of enrollment, the severity of the AEs and drug adjustments were performed according to the investigator’s discretion.

- - - 1. **Causality to study drugs**

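### The organ-toxicity stop in the non-haematological grade IV row is triggered by grade V, which the protocol defines as death, so it can never operate

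*Protocol*

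**What the plan says.** The table in protocol section 7.2 (Dose Adjustment Criteria) gives one row per toxicity grade. The non-haematological grade IV row has two parts. The general rule is: "Drug interruption and symptomatic treatment should be provided, and the dose is reduced by one level if AE resolves to grade <I". A further clause then covers particular organs: "Drug interruption is recommended if a grade V AE occurs (such as Grade V kidney injury, neurotoxicity, cardiotoxicity, hepatotoxicity, and other life-threatening".

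The grades are defined in section 10.2 (AEs grade): "Grade IV is defined as life-threatening consequences" and "Grade V is defined as death related to AE". Table 7.4.1, which is headed as NCI-CTC AE 4.0, uses the same meanings for hypertension.

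The last row of the section 7.2 table covers adverse events of special interest: certain haemorrhages, arterial thrombosis, grade IV venous thrombosis, leukoencephalopathy syndrome and gastrointestinal perforation. For these, "drug interruption is recommended and aggressive symptomatic treatment should be provided".

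Section 7.4 gives event-specific rules. Grade IV hypertension calls for "Immediate and permanent drug discontinuation". For renal insufficiency or nephrotic syndrome, "the drug must be discontinued immediately and aggressive symptomatic treatment must be administered". For arterial thrombosis, "drug administration should be discontinued immediately and the study should be withdrawn".

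**The concern.** A clause that names kidney, nerve, heart and liver toxicity and calls them life-threatening is evidently meant to treat them more strictly than other grade IV events. Tied to grade V, it has no case to which it can apply. A site that follows the table then falls back on the general grade IV rule, which returns a recovered patient to anlotinib (or placebo) one level lower.

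Changing the grade alone would not repair it. The row already opens by interrupting the drug for every grade IV event, so a second instruction to interrupt at grade IV would add nothing. The clause has content only as a permanent stop.

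What is at stake is the written default for a patient who has survived a life-threatening organ toxicity, and consistent handling across sites, which section 7.2 gives as the reason for the table.

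**Working it through.** No planned figure depends on this point, so the check is mainly a reading of the rules against each other.

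**Step 1: can the clause operate?** Trigger: grade V (section 7.2, grade IV row, written twice). Meaning of grade V: death (section 10.2 and Table 7.4.1). The section 10.2 definitions are offered for events not listed in CTCAE, but Table 7.4.1 applies the same meaning under the CTCAE heading. No dosing decision remains after death, so the clause never operates. Its closing reference to life-threatening events matches the definition of grade IV, and it stands in the grade IV row. That grade IV was intended is an inference; what the text says is grade V.

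**Step 2: what rule is left?** Take a grade IV hepatic event at the starting dose:

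- interrupt and treat (grade IV row, general part);
- hold for at most 6 weeks per cycle (section 7.2 text);
- if it resolves to below grade I, which read literally means full resolution, resume one level lower: 12 to 10 mg, or 10 to 8 mg if already reduced (section 7.1);
- from 8 mg, the next step is discontinuation (section 7.1).

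**Step 3: which organs have a stop elsewhere?** Section 7.4 has 10 headings: fatigue, diarrhoea, hypertension, hand-foot skin reaction, proteinuria, bleeding, thrombus, RPLS (reversible posterior leukoencephalopathy syndrome), abdominal pain and pulmonary interstitial fibrosis.

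| Organ named in the clause | Working stop in section 7.4 | What is left uncovered |
| --- | --- | --- |
| Kidney | Renal insufficiency, nephrotic syndrome | Other grade IV kidney events |
| Heart | Arterial thrombosis, including infarction and angina | Other grade IV cardiac events |
| Nervous system | Arterial thrombosis including stroke; RPLS | Other grade IV neurotoxicity |
| Liver | None | All grade IV hepatic events |

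Three of the four organs have a partial stop; one has none.

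**Step 4: special-interest row against section 7.4.**

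| Event | Section 7.2 table | Section 7.4 |
| --- | --- | --- |
| Arterial thrombosis | Interruption | Immediate discontinuation and withdrawal |
| Symptomatic grade IV venous thrombosis | Interruption | Discontinuation and withdrawal |
| Asymptomatic grade IV venous thrombosis | Interruption | Stop, anticoagulate, may resume at a reduced dose |
| Gastrointestinal perforation | Interruption | Immediate discontinuation and withdrawal |
| Leukoencephalopathy syndrome | Interruption | Discontinuation on suspicion; withdrawal once confirmed by imaging |

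The table is weaker than section 7.4 in every line except asymptomatic venous thrombosis.

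**Step 5: how often might it matter?** Table 3 of the protocol (12 mg, N=21, whole study) gives grade III ALT 0/21, AST 0/21 and direct bilirubin 1/21; grade I/II ALT 10/21 and total bilirubin 8/21. Exact (Clopper-Pearson) 95% limits:

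- 0/21: upper limit = 1 − 0.025^(1/21) = 0.161, so 0 to 16.1%.
- 1/21 = 4.8%: lower limit = 1 − 0.975^(1/21) = 0.001; the upper limit solves P(X ≤ 1) = 0.025 and is 0.238, so 0.1 to 23.8%.

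Table 3 has no grade IV column, so no grade IV hepatic rate can be derived. The only hepatic experience the protocol reports for a gefitinib combination (section 1.1, apatinib plus gefitinib) is grade 3 transaminase elevation in 2 of 12 patients, both recovered after a pause without dose reduction. That is a different drug. It shows that liver toxicity is relevant, not how often it will occur here.

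**The case against.** **The wording is loose throughout.** The translated text does not keep interruption and discontinuation apart: section 7.4 speaks of discontinuing for diarrhoea and for grade III venous thrombosis, and then of resuming. This stands, and it means that no conclusion should rest on the word interruption alone. It does not rescue the clause, whose defect is the trigger grade.

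**The grade III row may already cover it.** That row ends by recommending interruption for reactions of grade 3 or above. If interruption meant a permanent stop, this sentence would reach living grade IV patients. But it names no organ, and it does not displace the explicit reduce-and-resume rule in the grade IV row.

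**Restart after a recovered grade IV event is not unusual here.** Section 7.4 resumes at reduced dose after grade 3-4 diarrhoea and after asymptomatic grade IV venous thrombosis. This is true, so restart is not wrong in itself. The point is that the protocol singles out these organs for a stricter rule and then gives a rule that cannot apply.

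**Other safeguards exist.** Restart requires resolution to below grade I. Sections 5.5, 6.2 and 7.4 allow termination for toxicity not tolerated after dose adjustment, discontinuation on the investigator's judgment, and management according to the clinical situation. All of this stands. A reader might infer that the protocol forces re-exposure after any grade IV organ toxicity; these provisions show that it does not. A reader might also infer that all four organs are left without a stop; section 7.4 shows otherwise for three of them.

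**A gap in the grade III row.** A reader might infer that nothing is specified when a grade III event takes between 2 and 6 weeks to recover. The section 7.2 text does give a general rule: suspension up to 6 weeks, then restart at the original or a lower dose. There is no such gap.

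**Conclusion.** The clause is wrong as written. Its trigger is death, so it can never apply. A grade IV kidney, neurological, cardiac or hepatic event without its own rule in section 7.4, which means chiefly a hepatic one, is by default interrupted and, if it resolves to below grade I within the 6-week hold, resumed one level lower, subject to investigator judgment. The special-interest row separately understates what section 7.4 orders for arterial thrombosis, symptomatic grade IV venous thrombosis, perforation and leukoencephalopathy syndrome.

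That the clause cannot operate follows from the protocol's own definitions. That grade IV and a permanent stop were intended is an inference from the clause's position, its reference to life-threatening events, and the fact that interruption is already required at grade IV.

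The consequence is for patient safety and consistency between sites. The frequency is probably low and no patient count can be given. A reader might go further and infer a bias in PFS; nothing in the protocol supports that, and none is claimed. The error should be corrected because it sits in an operative safety rule and the correction is cheap.

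**What to change.** 1. **Non-haematological grade IV row.** Change grade V to grade IV in both places. For the life-threatening kidney, neurological, cardiac, hepatic and other toxicities the clause names, replace the recommendation to interrupt by a recommendation to discontinue anlotinib/placebo permanently. Other grade IV events keep the interrupt-and-reduce rule. Add that events with their own rule in section 7.4 follow section 7.4.
2. **Special-interest row.** Align it with section 7.4: discontinuation and withdrawal for arterial thrombosis, symptomatic grade IV venous thrombosis and gastrointestinal perforation; for leukoencephalopathy syndrome, discontinuation on suspicion and withdrawal once confirmed by imaging. Asymptomatic grade IV venous thrombosis stays under its existing rule in section 7.4.

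Check the source-language text at the same time, since the slip may have arisen in translation. The cost is the wording of two table rows and the filing with the ethics committee that section 11.1 requires for any modification. Design, sample size and analysis are unchanged.

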In the event of pulmonary symptoms (dyspnea, cough, and fever) gefitinib therapy should be interrupted, and a prompt investigation of these symptoms should occur. If interstitial lung disease is confirmed, gefitinib should be discontinued and appropriate treatment should be conducted.

No dosage adjustment is recommended for patients with different body weights, gender, ethnicity, renal function, or moderate to severe hepatic impairment due to liver metastases.

For patients treated with gefitinib combined with anlotinib who discontinue gefitinib therapy, the decision of proceeding with anlotinib is determined by the investigator.

When AEs occur, dose adjustment of gefitinib and subsequent dosing regimens are determined by the investigator.

- 1. **Management of anlotinib-related AEs**

Management of anlotinib-related AEs will be performed by the investigator based on the actual clinical situation (reference the following management).

1. **Fatigue**

Fatigue is often associated with oncologic treatment, and it is recommended to monitor the onset of severe fatigue by observation and documentation of the patient's fatigue. No dosage adjustment is necessary if grade 1-2 fatigue occurs; aggressive symptomatic treatment should be provided if grade 3-4 fatigue occurs. In absence of jaundice, thrombi, and pregnancy, progesterone drugs (such as megestrol) and multivitamins may be administered to help reduce fatigue and enhance physical performance. In addition, care must always be taken to identify other causes of fatigue such as those secondary to hypothyroidism, depression, anemia, or pain.

1. **Diarrhea**

Diarrhea may impact the digestive function, fluid and electrolyte balance of the patient, and the absorption of medications, early treatment should be performed. Diarrhea usually appears during the first few days of treatment. No dosage adjustment of anlotinib should be performed.

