No dose adjustment of anlotinib should be required if grade 1-2 diarrhea occurs, and patients are recommended to: regulate dietary habits, drink more water, and eat easily digestible, absorbed, and vitamin-rich food; avoid intake of diarrhea-inducing diets (e.g., greasy, spicy foods, and coffee) or undergo medications such as stool softeners and gastrointestinal prokinetic agents; increase the diet with plenty of dietary fiber and administer micro-ecological drugs (e.g., bifid triple viable). Among them, when grade 2 diarrhea occurs, loperamide, diphenoxylate, gastric mucosal protective agents (montmorillonite powder), and berberine can be appropriately administered. Aggressive symptomatic treatment should be performed if grade 3-4 diarrhea occurs, and care must always be taken to replenish water and electrolytes to maintain fluid and electrolyte balance and provide acid-base disturbance. Immediately discontinue anlotinib until diarrhea is significantly reduced or ceases, and reduce the dose appropriate when restoring drugs.

1. **Hypertension**

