Hypertension is emerging as one of the most common AEs. The [cardiovascular toxicities](https://www.sciencedirect.com/topics/medicine-and-dentistry/cardiovascular-toxicity) panel of the NCI recommends that patients with hypertension at baseline should be diagnosed before VEGF/VEGFR-inhibitor therapy, and patients should have a sustained blood pressure of <140/90 mmHg during the treatment. Blood pressure (BP) should be performed monitored before administration of the drug and especially in the first 2 weeks of treatment (daily monitoring should be performed), and monitoring must continue throughout treatment. Therefore, for patients with hypertension, the antihypertensive drugs should be administered based on individualized principles before receiving anlotinib to achieve early and favorable BP control (BP of ≤140/90 mmHg). However, prophylactic antihypertensive therapy is not recommended for patients with normal BP. Patients should be adequately informed to contact the investigator immediately for guidance when BP is >140/90 mmHg or when symptoms associated with elevated BP occur (e.g., significant headache, dizziness, visual disturbances, etc.). It has been suggested that antihypertensive drugs should be chosen according to the 2010 Chinese guidelines for the management of hypertension, regarding the risk factors for cardiovascular disease in patients. For patients combined with proteinuria, an angiotensin-converting enzyme inhibitor (ACEI) or an angiotensin receptor blocker (ARB) is recommended. A word of caution in drug selection is required that anlotinib is primarily metabolized by the lung CYP3A4 enzyme. Non-dihydropyridine calcium channel blockers (verapamil and diltiazem) can moderate CYP3A4 inhibition and are not recommended for BP control.

If a grade 3-4 increase in BP occurs, antihypertensive treatment or dose modification of this product should be performed under the guidance of the specialist. Drug discontinuation is recommended if the adverse reaction persists. This product should be permanently discontinued in patients who develop a hypertensive crisis. Recommendations for the prevention and treatment of anlotinib-associated hypertension can be viewed in **Table 7.4.1** hypertension classification criteria (NCI-CTC AE 4.0) and recommendations for prevention and treatment.

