The incidence of HFSR decreased with increasing treatment duration in the treatment period. Discontinuing the drug if grade >2 AEs appears three times and tends to worsen, and continue drug treatment if AE resolves to normal or grade 1; If HFSR has no further occurrence, the dose of anlotinib should progressively increase until the standard dose; If grade >2 AEs reoccurs after the resumption of dosing, it is recommended to continue dosing after a dose reducing by one level; If grade 3 of AEs persists or tend to worsen, permanent discontinuation of anlotinib is recommended. Recommendations for the prevention and treatment of anlotinib-associated HFSR can be viewed in **Table 7.4.2** HFSR classification criteria (NCI-CTC AE 4.0) and recommendations for prevention and treatment.

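### Section 7.4 gives conflicting anlotinib dose actions for the same event, most clearly for grade 3 hand-foot skin reaction

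*Protocol*

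**What the plan says.** **HFSR.** The section 7.4 text reads: "Discontinuing the drug if grade >2 AEs appears three times and tends to worsen". It allows resumption after recovery to normal or grade 1. It then has the dose rise step by step to the standard dose if HFSR does not come back, and recommends a one-level reduction if grade >2 recurs after resumption. It recommends permanent discontinuation if grade 3 persists or tends to worsen. Table 7.4.2, grade 3, suspends anlotinib and then has: "Administering a lower dose of anlotinib if symptoms resolve".

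**Hypertension.** The section 7.4 text reads: "If a grade 3-4 increase in BP occurs, antihypertensive treatment or dose modification of this product should be performed", with a specialist guiding the choice. It recommends discontinuation if the reaction persists, requires permanent discontinuation for hypertensive crisis, and refers the reader to Table 7.4.1. In that table, grade III is suspension followed by: "Continue the drug treatment at a dose reduced by one level with well-controlled blood event". Grade IV is immediate permanent discontinuation.

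**Diarrhoea.** The first paragraph of the item ends: "No dosage adjustment of anlotinib should be performed". The next paragraph applies no adjustment to grades 1-2 and says for grades 3-4: "Immediately discontinue anlotinib until diarrhea is significantly reduced or ceases, and reduce the dose appropriate when restoring drugs".

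**General rules.** In the Dose Adjustment Criteria of section 7.2, the grade III non-haematological row interrupts the drug and, on recovery within two weeks, has: "continue drug treatment with the original dose level or at a dose reduced by one level by the investigator's discretion". Section 7.2 also says that a patient cannot go back to the earlier dosing after a reduction, and that its criteria are there to keep dose adjustment consistent.

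**The concern.** Two investigators with the same patient and the same grade could both follow section 7.4 and give different doses: one by reading the text, the other by reading the table. No sentence says whether the text, the event table or the general criteria prevail.

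Two things are at stake. The first is patient safety, since the sources differ on whether drug is held at a first grade 3 event. The second is consistency of the tested regimen. Whether a reduction is made, and whether it can be reversed, shapes later dose intensity. If sites settle the question differently, the safety tables and the delivered dose reflect which page was followed as well as the toxicity itself.

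**Working it through.** The plan states no figure to reproduce. The check is to take each event and read off the action from each source.

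**1. A first episode of grade 3 HFSR that settles**

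| Source | Hold the drug? | Dose on resumption |
|---|---|---|
| 7.4 text | Stop tied to grade >2 three times with worsening; permanent stop if grade 3 persists or worsens | Reduction by one level stated for recurrence after resumption |
| Table 7.4.2 | Suspend at grade 3 | Lower dose once symptoms resolve |
| 7.2 general row, grade III | Interrupt | Original or one level lower, at discretion |

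For this patient neither stopping condition in the text is met and its stated trigger for reduction has not occurred. The table both suspends and reduces. The two differ on whether to hold and on what triggers a reduction.

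**2. Re-escalation after HFSR**

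Take the standard dose to be the 12 mg/day starting dose, and suppose a patient has been reduced to 10 mg/day, the first reduction level in section 7.1. If HFSR does not return, the 7.4 text moves the dose back up towards 12 mg. Section 7.2 does not allow that. The two instructions cannot both be followed.

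**3. Hypertension**

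| Source | Grade 3 | Grade 4 |
|---|---|---|
| 7.4 text | Antihypertensive treatment *or* dose modification, with specialist guidance | Same sentence; permanent stop for hypertensive crisis |
| Table 7.4.1 | Suspend, then one level lower | Immediate permanent stop |
| 7.2 general row | Interrupt, then original or one level lower | Interrupt, then one level lower |

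The text's alternative can be met by antihypertensive treatment alone. The grade III row of the table offers no such alternative. The general grade III row also permits restart at the original dose, which Table 7.4.1 does not. At grade 4 the text and the table partly agree, because the table's grade IV definition includes hypertensive emergencies and the text stops permanently for hypertensive crisis.

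**4. Diarrhoea**

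The closing sentence of the first paragraph has no grade limit, so read literally it covers grades 3-4. The following paragraph stops the drug and lowers the dose at those grades.

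**5. Illustrative counts**

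Inputs: 155 patients per arm (section 3.3); 13.2% grade 3-5 hypertension and 3.7% dermal toxicity from the phase III study cited in section 1.1; 2/21 grade III raised blood pressure, 1/21 grade III hand-foot skin reaction and 0/21 grade III diarrhoea over the whole study process in the 12 mg cohort (Table 3).

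Expected count = 155 × rate:
- hypertension, cited study: 155 × 0.132 = 20.5
- raised blood pressure, 12 mg cohort: 155 × 2/21 = 14.8
- dermal toxicity, cited study: 155 × 0.037 = 5.7
- hand-foot skin reaction, 12 mg cohort: 155 × 1/21 = 7.4
- diarrhoea, 12 mg cohort: 155 × 0/21 = 0

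**The case against.** The strongest reply is that section 7.4 is guidance. It opens by leaving management to the investigator according to the clinical situation, offers what follows as reference, and heads its tables as recommendations. That stands, and it lowers the severity. It does not remove the problem: discretion among stated options is different from two opposing instructions for one event, and section 7.2 says its criteria exist to make dose adjustment consistent.

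Several stronger readings are tempting, and the protocol does not support them.

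- *The HFSR text stops the drug only after three occurrences.* It also recommends permanent discontinuation if grade 3 persists or worsens. Its re-escalation sentence may also presuppose a restart below the standard dose, so recurrence need not be the only route to a lower dose.
- *A first reduction fixes the rest of the patient's dosing.* That follows from section 7.2 alone. The HFSR text says the opposite, and the protocol does not settle which holds.
- *Grade 3 hypertension has three opposing rules.* The general row overlaps with Table 7.4.1, since a one-level reduction lies within its range. Dose modification in the text can include suspension, and the text points to the table. Unchanged dosing is a possible reading and is not ordered.
- *Grade 2 HFSR is also in conflict.* Table 7.4.2 has dose adjustment as appropriate. The general grade II row keeps the original dose after any interruption, but section 7.2 also has suspension and reduction considered for grade 2 non-haematological toxicity, which fits the table.
- *The diarrhoea item contradicts itself throughout.* It is one loose sentence, and the next paragraph narrows it.

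**Conclusion.** The inconsistency holds, with unequal strength. HFSR is the clear case: text and Table 7.4.2 differ on when to suspend and when to reduce, and the text's re-escalation conflicts with section 7.2. Hypertension is milder and rests on reading the alternative in the text as permission to leave the dose unchanged. Diarrhoea is a minor wording fault.

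The contradictions are on the face of the text and depend on no event rate. The counts of about 20 and 6 only indicate how often such events might arise. They assume that rates from another study carry over to a gefitinib combination. The hypertension figure covers grades 3-5, and dermal toxicity is not HFSR alone. The 12 mg cohort is small. The documents give no basis for quantifying the effect on dose intensity, and none is claimed. The point should be corrected, but it does not by itself undermine the trial.

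**What to change.** The sponsor should set side by side the dose rules of section 7.2 (including the no-return rule and the Dose Adjustment Criteria), the section 7.4 text on diarrhoea, hypertension and HFSR, and Tables 7.4.1 and 7.4.2. These should be reconciled so that each event and grade has one consistent dose action and the protocol has one re-escalation rule. The sentences that conflict with the result should be removed, and the protocol should say which source governs if a difference remains. Which action applies, and which source governs, is for the sponsor to decide.

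The cost is amendment wording and site training, with no added visits or tests.
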